### Statistical analyses

Missing values will be imputed. Intent-to-treat as well as completer analyses will be conducted. The effect of the intervention is analyzed with a chi-square test on the dichotomous primary outcome measure, presence of the depression diagnosis (K-SADS-PL). The cost-effectiveness analyses will be based on the comparison of costs and effects in both conditions and will be done according the international guidelines [70]. The cost- effectiveness analyses will be done separately from the perspective of mental health and society over a period of 6 months and 1 year. The effects of societal costs will be expressed in years to live, corrected for quality of life (QALYs). The costs of CBT versus CAU will be expressed in 1) incremental costs per QALY and 2) incremental costs per adolescent with a depression in full remission.

The secondary continuous outcome measures will be analyzed with repeated measures MANCOVA using the pre-test as a covariate as is recommended for RCT’s with pre-, post- and follow-up measurements [71]. For each questionnaire, the effect size (Cohen’s d) from pre- to post-treatment is defined as (M_pre_-M_post_)/SD_pooled_, where SD_pooled_ = [(SD_pre_^2^ + SD_post_^2^)/2]. CBT versus TAU pre-post effect sizes are calculated as follows [(M_CBT post_-M_TAU post_)/SD_pooled post_] – [ (M_CBT pre_-M_TAU pre_)/SD_pooled pre_]. Furthermore, analyzes will be conducted to establish clinical significance and the reliable change index [72].

Moderators will be analysed by multi-group analyses for dichotomous variables. The continuous variables will be analysed using hierarchic regression analyses. Mediator effects will be analysed using hierarchical regression analyses and structural equation modelling.

## Discussion

As Weisz [13] pointed out, it is not enough to replicate studies to increase our knowledge of effective treatment of adolescent depression. It is necessary to be innovative and to go further and “pushing the boundaries of what has been done” [13]. In this study the design is innovative in several regards.

First, the target population consists of referred clinically depressed adolescents and the treatment is conducted within routine mental health care services with routine care professionals, in the Netherlands. Therefore, CBT is investigated under real life conditions.

Second, the control condition is an active condition, namely treatment as usual (TAU) within routine clinical care, not a waiting list condition or just one specific treatment such as medication. TAU being the control condition is a more rigorous test of effectiveness of CBT. As a secondary spin off, the collected data will also enable a detailed description of TAU without CBT.

Third, long term effects of CBT versus TAU will be examined, up to one year post treatment. This is important because of possible sleeper effects [73] and recurrence of depressive symptoms.

Fourth, cost-effectiveness was investigated for a group CBT program “Coping with Stress”, but only in adolescents with a subclinical depression and as a prevention program [24]. Cost-effectiveness of CBT versus TAU in adolescents with clinical depression to our knowledge is not yet investigated. Also productivity losses have never been taken into account. The cost-effectiveness is of increased importance because of diminishing budgets in mental health care. Perhaps even more important, in this study the costs of clinical depression in adolescents are determined.

Fifth, although it is very important to know why a treatment works and for whom it works, few studies actually addressed this topic. In this study potential mediators and moderators will be investigated.

As a result of the design, we anticipate several problems, which may become limitations of this study if not properly addressed. To ensure the quality of the study, these problems and their solutions, which are undertaken to minimize the limitations, are discussed.

First, content of TAU and the techniques used are difficult to monitor. Assessment of the therapeutic procedures used during each session by the therapist, provides detailed information on the components of the treatment. Also two sessions are recorded at random, observed and rated in detail to assess content of treatment and techniques used.

Second, comparing CBT to an active control condition may lead to a lower mean effect size than CBT versus a non-active control condition [13]. The TAU condition in this study is heterogeneous and it contains also evidence-based treatments such as Interpersonal therapy. As a result the ES can be even smaller, so we increased the power accordingly.

Third, to include 140 adolescents within 18 months, cooperation with a large group of mental health institutions is necessary. Furthermore, we try to minimize the effort the adolescent and their parents have to put into the study by using online assessments of the self-report questionnaires, while ensuring secrecy. Since the K-SADS-PL is assessed in vivo, not only self-report, but also observations by an independent clinician are taken into account.

Fourth, non-response may be a huge problem because of the multiple assessments and informants. Online assessment enables the researchers to monitor the progress per assessment per informant. They can react immediately to non-response and increase the response rate accordingly. This transparent logistic process of data collection, data transportation and data file construction reduces the risk of mistakes, missing data and contributes to the quality of the data [74].

Fifth, as it is not allowed to conduct CBT within the TAU condition it is inevitable that TAU is changed in this regard. This is a methodological problem, which may lead to bias, but cannot be solved properly. Although we are fully aware of this methodological problem we accept it because of the advantages of an RCT in a naturalistic setting. The preferred choice of treatment by the multidisciplinary team for every included depressed adolescent is registered and enables us to take into account the preferred choice of treatment.

Sixth, the total amount of face-to-face contact within TAU can be different from CBT. Also the time period in which the treatment is completed can differ within TAU and CBT. The amount of face-to-face contact in minutes and the time period of the treatment will be taken into account as potential moderating factors.

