## Background

Depressive disorders in adolescents are among the most prevalent disorders with a high burden of disease [1] and high risk of recurrence [2,3]. Before entering adulthood, 14 to 25% of the adolescents have experienced at least one episode of a depressive disorder [2]. Besides the high prevalence [4-7], comorbid psychiatric diagnoses are often present [8-10]. In addition, a heightened risk exists for development of social problems, juridical problems, learning problems, substance abuse, negative life events, physical problems, teen pregnancies and suicide [2,9,11]. Therefore, it is important that depression is treated in an early stage with an effective treatment [2,12].

In the international literature, there is no consensus on the degree of effectiveness of psychotherapeutic interventions in depressed adolescents. In a meta-analysis, which included studies with a large diversity of investigated interventions, only a modest effect size of 0.34 was found [13]. Other meta-analyses calculated medium (0.72) [14] to large (1.27) effect sizes [15]. In a meta-analysis solely directed at Cognitive Behavioral Therapy (CBT) a medium effect size of 0.53 was found [16]. Although the effect size for CBT is promising, it also reflects the need for improved treatment of depression, as a large group of depressed adolescents will not recover after CBT treatment.

In addition, it is often discussed that effectiveness studies in depressed adolescents lack generalizability for clinical practice, because the study samples do not match the complex and severe cases in routine mental health care [13]. In this study, this issue is addressed by comparing CBT to treatment as usual within a referred clinically depressed group of adolescents.

Within this study an individual revision of the group CBT program “Coping with Depression course for Adolescents” (CWD-A) [17] will be investigated. Group CBT was adapted into an individual CBT format because it is much better applicable within mental health care than group CBT, for instance children can start treatment immediately. Several RCT’s were conducted with an American population, but not with clinically referred adolescents. Results repeatedly have shown that the CWD-A was more effective than control conditions [18,19] and treatment as usual [20,21]. As only one research group investigated the CWD-A, it is regarded as probably efficacious [22].

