#### Sample size

Based on previous research [16] an effect size (Cohen’s d) of 0.53 is expected. Power calculations indicated that 70 adolescents per condition (assuming an alpha of 0.05, a statistical power, 1-beta, of 0.80 and a drop-out of 20%; power calculations in STATA) are required to detect a difference in depression diagnosis. In total 140 adolescents will be included.

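### The Discussion says power was raised to allow for a smaller effect against active TAU, but the documented sample size contains no such increase

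*Protocol article*

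**What the plan says.** The Discussion of the protocol article lists anticipated problems together with the steps taken against them. The second is that an active control may lower the mean effect size. TAU here is mixed and includes evidence-based treatments such as interpersonal therapy. The item ends: "As a result the ES can be even smaller, so we increased the power accordingly".

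The Sample size section gives the calculation itself. On the basis of reference 16, "an effect size (Cohen’s d) of 0.53 is expected". The remaining inputs are "assuming an alpha of 0.05, a statistical power, 1-beta, of 0.80 and a drop-out of 20%; power calculations in STATA", and the result is 70 adolescents per condition, 140 in total.

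The Background shows where the effect size comes from. It attributes a value of 0.53 to a meta-analysis of CBT alone, citing the same reference 16. It also reports that in a broader meta-analysis of many kinds of intervention "only a modest effect size of 0.34 was found".

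Under Statistical analyses, the primary test is a chi-square on presence of the depression diagnosis (K-SADS-PL).

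**The concern.** The Discussion sentence reads as a fact about the design: a threat was foreseen and the trial was strengthened against it. A strengthened design would show a smaller effect than the published one, a power above 0.80, or more participants than the basic calculation needs. The Sample size section appears to show none of these.

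What is at stake is how the result is read. If the trial finds no significant difference, a reader who relies on the Discussion would believe that dilution by active TAU had been covered, and would give the null result more weight than the documented sample supports.

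**Working it through.** **Inputs.** From Sample size: d = 0.53 (so SD = 1), alpha 0.05, power 0.80, drop-out 20%, 70 per arm. The sidedness of the test is not stated, and two-sided is assumed.

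**Step 1: reproduce the plan's figure.** For two means,

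n per arm = 2 × (1.960 + 0.842)² / d² = 2 × 7.849 / 0.2809 = 55.9, rounded up to 56.

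With 20% drop-out, 56 / 0.80 = 70 per arm, or 140 in total. This matches exactly. The t-based version needs 57 evaluable and 72 recruited per arm, slightly more than planned.

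**Step 2: look for a reserve.** Planned 70 minus required 70 leaves 0 per arm. With 56 evaluable per arm, the smallest effect detectable at 80% power is (1.960 + 0.842) × √(2/56) = 0.529, which is the design effect itself. The design effect also equals the Background figure (0.53 in both places, same reference), so it was not reduced.

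**Step 3: what an increase would have looked like** (normal approximation, then divided by 0.80).

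| Design | Evaluable per arm | Recruited per arm | Total |
|---|---|---|---|
| d = 0.53, 80% power (as documented) | 56 | 70 | 140 |
| d = 0.53, 90% power | 75 | 94 | 188 |
| d = 0.50, 80% power | 63 | 79 | 158 |
| d = 0.45, 80% power | 78 | 98 | 196 |
| d = 0.34, 80% power | 136 | 170 | 340 |

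Every strengthened version exceeds 140.

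**Step 4: sensitivity of the documented sample, for illustration.** The value 0.34 is the Background's broad meta-analysis figure, and 0.45 is an assumed intermediate value.

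*Continuous measure, two-sided t-test, 56 per arm:* power is 0.79 at d = 0.53, 0.66 at 0.45 and 0.43 at 0.34.

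*Binary primary outcome, 56 per arm.* The conversion is ln(OR) = d × π/√3, which gives OR = 2.62 for d = 0.53 and OR = 1.85 for d = 0.34. Power is for the two-proportion test without continuity correction. The TAU diagnosis-free rates are assumed.

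| TAU diagnosis-free | CBT at d = 0.53 | Power | CBT at d = 0.34 | Power |
|---|---|---|---|---|
| 30% | 52.8% | 0.69 | 44.3% | 0.34 |
| 40% | 63.5% | 0.71 | 55.3% | 0.36 |
| 50% | 72.3% | 0.68 | 64.9% | 0.36 |
| 60% | 79.7% | 0.62 | 73.5% | 0.33 |
| 70% | 85.9% | 0.53 | 81.2% | 0.28 |

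The test that decides the trial therefore shows no hidden reserve either.

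**The case against.** Several readings could rescue the sentence.

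- **A one-sided test.** This would need 45 evaluable and 57 recruited per arm (t-based), leaving slack. But the article mentions no one-sided test, it does not reproduce 70, and 56 evaluable would then give power of about 0.88 where the text states "a statistical power, 1-beta, of 0.80".
- **The drop-out allowance is the increase.** The Sample size section assigns it to drop-out. Even with no drop-out, 70 per arm gives t-test power of only 0.75 at d = 0.45.
- **Power was raised from an earlier, unpublished design.** This cannot be excluded. It would not change the documented result, which is 80% power at the unreduced effect.
- **The 0.53 may already reflect active controls.** That cannot be checked from the article. The Discussion nevertheless says the effect can be smaller and that power was raised in response.

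A reader might go further and infer that the article expects an effect well below 0.53, and so a trial far below 80% power. The text does not support that. It says only that the effect may or can be smaller, and the one effect it calls expected is 0.53. The 0.34 comes from a diverse set of interventions, not from CBT against active TAU. Nor does the article say that a null result would be read as equivalence.

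It is also fair to say that nothing is miscalculated, since 56/0.80 is 70. The defect is that two statements disagree.

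**Conclusion.** The point holds. The Discussion claims an increase in power that the Sample size section does not contain. All 140 participants are accounted for by d = 0.53, 80% power and 20% drop-out, leaving a reserve of zero. This conclusion assumes a two-sided test, which is the reading that reproduces the stated figure.

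The loss of power at smaller effects is illustrative. It depends on the assumed effect and, for the primary outcome, on the logistic conversion and the assumed TAU diagnosis-free rate. The claim that an increase was never made at any stage goes further than the article allows. What can be said is that the documented design shows none.

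**What to change.** Either delete the claim of increased power from the Discussion, or, if an increase was made, state the reduced effect or the higher power in the Sample size section with the number of participants that matches it.

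If the total stays at 140, replace the claim with wording such as: *The documented sample size has no reserve for an effect smaller than d = 0.53.* Follow it with the sensitivity of the actual primary test, the chi-square on diagnosis, naming the assumed TAU diagnosis-free rate and the conversion used. Continuous-measure power alone would describe a different analysis from the primary one. A sentence saying that a non-significant result will be read through the confidence interval and not as equivalence would be useful but is optional.

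If the sample stays at 140, the cost is wording and a less favourable stated sensitivity, with no change to the endpoint or the analysis. Building in a real increase would cost participants: for example 188 in total for 90% power at d = 0.53, or 196 for 80% power at an assumed d = 0.45, both on the continuous-measure calculation.

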#### Aim of the study

The aim of this study is to investigate the effectiveness and the cost-effectiveness of the individual CBT program the “D(o)epression course” in a sample of referred adolescents with a Depressive Disorder according to DSM-IV-TR [25] in a randomized controlled trial. We expect that CBT will be more effective than TAU (without CBT). Furthermore, cost-effectiveness of CBT and the cost of illness of clinical depression in adolescents will be established. Potential moderators (comorbidity, severity of depression, age, ethnicity, gender, suicidal thoughts and psychopathology in parents) and mediators (negative automatic thoughts, cognitive emotion regulation and attribution style) for the effectiveness of CBT will be studied. The role of non-specific treatment variables (therapeutic alliance, client expectancy, client satisfaction, treatment adherence) will be taken into account as well (see Figure 1).

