#### Design

This study is designed as a multi-site, randomized controlled clinical trial in which individual CBT will be compared to TAU. Four multiple informant (adolescent, parent, therapist) assessments are done: prior to treatment (pre-test assessment), immediately after treatment (post-test assessment or after 15 sessions), 6 months after treatment (6 month follow-up) and 1 year after treatment (1 year follow-up). To investigate potential mediators two temporary assessments are conducted, each after 5 therapy sessions.

All sessions will take place within routine outpatient care within second order public mental health clinics to enhance external validity. All treatments in both conditions are delivered by psychologists with at least a master's degree-level and two years of experience within professional mental health care. These professionals are trained before delivering the treatments to enhance treatment integrity.

Adolescents who are diagnosed with a depression according to the K-SADS-PL [26,27], who meet inclusion criteria and do not meet the exclusion criteria are randomly assigned to either individual CBT or TAU. Random assignment per adolescent is executed using computer generated block randomisation and stratified per mental health centre. See Figure 2 for patient’s flow chart.

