#### Intervention

The experimental treatment is a protocolled individual CBT program, the D(o)epressie course. It consists of 15 weekly sessions of 45 minutes, two parent sessions after 3 and 9 weeks and a meeting with the parent at the end of treatment. The D(o)epressie course is, as the CWD-A, based on the social learning theory about the aetiology of depressions by Lewinsohn [28]. According to this theory, there is a connection between the number of positive interactions between a person and his environment on one hand, and depression on the other. A triggering event such as a stressful life event causes a negative spiral of less positive interactions leading to more negative thoughts and a deteriorating depressed mood. The aim of the intervention is to reduce depressive complaints in adolescents with a depressive disorder. Since depressive episodes are multi-factorial determined, the focus of the intervention is broad. The intervention contains representative components of CBT [29] namely: psycho-education (information about depression and the rationale for the aetiology of the complaints and the treatment of them), setting attainable goals (translate large goals into realistic short term goals), self monitoring (registration of the mood, activities and thoughts), activation (planning frequent, joyful activities), improving social skills and communication skills (improvement and stimulation of social behaviour), relaxation techniques, cognitive restructuring (identifying and changing unrealistic negative thoughts about the self, others and events), role play and problem solution skills (teaching the creation of solutions for problems via brainstorm, choosing, trying and evaluating) and relapse prevention. Exercises are executed within the sessions and are generalised into daily life by means of homework assignments. In the parent sessions, parents will receive psycho education and information on CBT. Therapists are not allowed to conduct treatments in both conditions.

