The economic evaluation is done by registration of costs in a cost diary based on the Trimbos Institute and Institute of Medical Technology Assessment Questionnaire on Costs Associated with Psychiatric Illness (TiC-P) [59] and PRODISQ [60]. The registered costs are directly related to health care or indirect health care (out-of-pocket costs, costs of informal care) and direct costs outside health care (monetary value of production losses caused by absence and reduced productivity). The costs will be considered separately from the perspective of mental health and from society. The mental health costs are the costs, which are credited to the mental health care budget, the decision-maker’s perspective. The societal costs are the costs of direct (mental) health care as well as indirect costs such as lost productivity, school absent and out-of-pocket costs.

Potential moderators that are analysed are severity of the depression, comorbidity, parental depression and psychopathology and demographic variables. Demographic information is gathered by adding questions about gender, age, ethnicity, education level and family income to the self-report questionnaires.

Three mediators are investigated namely negative automatic thoughts (CNCEQ) [61], cognitive emotion regulation (CERQ) [62] and attribution style (CASQ) [63]. The Cognitive Negative Cognitive Error Questionnaire (CNCEQ) measures cognitive errors namely the underestimation of the ability to cope, personalizing without mind reading, selective abstraction, over generalizing and mind reading. The Cognitive Emotion Regulation Questionnaire (CERQ) measures a broad set of cognitive emotion regulation strategies which are used in response to the experience of threatening or stressful life events; Self-blame, Other-blame, Rumination, Catastrophizing, Positive refocusing, Planning, Positive reappraisal, Putting into perspective and Acceptance. The Children’s Attributional Style Questionnaire (CASQ) is a self-report measure with three dimensions of attribution; internal- external, stable-unstable and global- specific.

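### Contact minutes and treatment duration are planned as moderators although both arise after randomisation, so interaction or adjusted effect estimates can be biased

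*Protocol article*

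**What the plan says.** The Discussion lists anticipated problems together with the measures taken against them. The sixth is that "the total amount of face-to-face contact within TAU can be different from CBT" and that "the time period in which the treatment is completed can differ within TAU and CBT". The measure against it is: "The amount of face-to-face contact in minutes and the time period of the treatment will be taken into account as potential moderating factors".

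The arms are built differently. Of the CBT course, the Intervention section says "It consists of 15 weekly sessions of 45 minutes", with parent sessions in addition. It gives no number of sessions for TAU, and the Discussion adds: "The TAU condition in this study is heterogeneous".

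Two lists of moderators stand elsewhere. Aim of the study has "Potential moderators (comorbidity, severity of depression, age, ethnicity, gender, suicidal thoughts and psychopathology in parents". Secondary outcome measures has "Potential moderators that are analysed are severity of the depression, comorbidity, parental depression and psychopathology and demographic variables". Neither contains contact minutes or duration. Under Statistical analyses, continuous moderators go into hierarchical regression, and the primary analysis is a chi-square test on the K-SADS-PL depression diagnosis.

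**The concern.** A moderator of a randomised effect should be fixed before allocation. At each of its values the two arms are then still exchangeable, and the difference between them is a treatment effect. Minutes received and weeks in treatment are not fixed in advance. They follow from the arm and may follow from the course of the illness. At equal duration, the CBT and TAU patients may then differ in prognosis, and their contrast no longer has the protection of randomisation.

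The protocol presents the question of for whom treatment works as one of the trial's innovations. An apparent finding that CBT does better in long treatments would bear directly on that question, and it could appear with no moderation at all. Nor does moderation answer the problem raised. Unequal contact is part of the contrast between the arms, and a subgroup or interaction analysis on received contact does not remove it.

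**Working it through.** The protocol gives no figure for this analysis and no size for any link between contact, arm and recovery. All correlations, shifts and slopes below are therefore assumptions, chosen to show direction and range.

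**Sample size, to fix the numbers.** Inputs from Sample size: d = 0.53, alpha 0.05 (two-sided assumed), power 0.80, drop-out 20%.
- n per arm = 2(1.96 + 0.8416)² / 0.53² = 55.9, rounded up to 56.
- 56 / 0.80 = 70, the stated figure.

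**Planned CBT contact** (Intervention): 15 × 45 = 675 minutes of adolescent sessions, parent sessions not counted. TAU has no corresponding figure.

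**Check 1: continuous outcome.** There are 56 completers per arm and the true effect is the same for everyone (0 or 0.53 SD). Minutes are in SD units, with correlation r with improvement within each arm and a mean shift in TAU. The model is outcome on arm, minutes and arm × minutes, with 5,000 runs and the interaction tested at 0.05. Results for a true effect of 0.53, where a negative r means that patients who improve less receive more contact:

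| Variable | r in CBT | r in TAU | TAU shift (SD) | Interaction rejects | Arm coefficient |
|---|---|---|---|---|---|
| fixed before randomisation | – | – | – | 4.9% | 0.53 |
| depends on arm only | 0 | 0 | 1 | 5.0% | 0.52 |
| same link in both arms | −0.3 | −0.3 | 1 | 4.8% | 0.18 |
| link in TAU only | 0 | −0.2 | 0.5 | 18.5% | 0.48 |
| link in TAU only | 0 | −0.3 | 0.5 | 35.5% | 0.46 |
| link in TAU only | 0 | −0.4 | 0.5 | 57.7% | 0.44 |
| link in TAU only | 0 | −0.5 | 0.5 | 77.6% | 0.41 |

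Two of these can be confirmed by hand.
- *Same link in both arms.* The slope of outcome on minutes is r. The CBT − TAU difference in mean minutes is −1 + r × 0.53 = −1 − 0.159 = −1.159. The adjusted arm effect is 0.53 − (−0.3)(−1.159) = 0.53 − 0.348 = 0.18. With a true effect of 0 it is 0 − (−0.3)(−1) = −0.30.
- *Link of −0.3 in TAU only.* The slopes differ by 0.3. The standard error is about √[(1 + 0.91)/56] = 0.185, so z is about 1.6. The power to detect a moderation that does not exist is then roughly 37%, close to the simulated 35.5%.

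**Check 2: diagnosis as outcome, no true effect.** There are 70 per arm. Prognosis u is standard normal and logit P(still depressed) = 1.0 × u in both arms. TAU duration is 15 + k·u weeks plus noise with SD 4. CBT duration is 15 weeks plus noise with SD 2, unrelated to u.

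| k (weeks per SD of prognosis) | CBT − TAU, 15 weeks or more | CBT − TAU, under 15 weeks |
|---|---|---|
| 2 | −7.6 points | +7.7 points |
| 4 | −12.1 points | +12.2 points |
| 6 | −14.2 points | +14.3 points |

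At k = 4 the interaction with continuous duration rejects 14.2% of the time. Splitting duration at 15 weeks gives about 15%, 28% and 41% for k = 2, 4 and 6. At k = 0 both tests stay near 5%.

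**Sensitivity of check 2.** If CBT duration has the same link and noise as TAU (k = 4, SD 4 in both arms), the subgroup differences are 0 and rejection is 4.3%. If CBT has k = 2 and SD 2, the subgroup differences are again 0, but the per-week interaction still rejects about 15%.

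**The case against.** The case on the other side is substantial.

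- **Recovery need not drive treatment length.** A reader might infer that allocation and recovery determine contact and duration. The protocol says only that they can differ by arm. It never says that TAU ends on recovery or continues without it. This stands: the link is plausible but assumed.
- **A false interaction is not inevitable.** A reader might infer that the analysis must create spurious subgroup effects. It does so only if the link with prognosis differs between arms. With dependence on arm alone, or the same dependence in both arms on the same scale, the test keeps about 5%. This stands too, but equal dependence does not rescue the plan: if the arms also differ in contact, the adjusted arm coefficient is biased.
- **CBT may vary as well.** The 675 minutes are a planned schedule. The protocol allows for 20% drop-out and measures adherence, so the claim that CBT has almost no spread is not supported.
- **The post-test timing may cap contact.** It is set at "immediately after treatment (post-test assessment or after 15 sessions". If that limits the sessions counted before the post-test, TAU contact by then is bounded, and the duration simulation has no such bound.
- **Scope is small.** This is one sentence in the Discussion, with no model or cut-point attached, and the Methods lists already leave both variables out. That lowers the priority. The sentence is nevertheless a stated remedy for a stated problem, not a detail left to an analysis plan.

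**Conclusion.** The point holds in a conditional form. The Discussion names two post-randomisation variables as moderators, and analysing them so can bias either the interaction or the adjusted arm effect. Which bias occurs, and how large it is, depends on relationships that the protocol does not give. Under the assumptions shown, false interaction rates run from the nominal 5% to about 14% in the middle duration scenario, and to 18.5–77.6% for TAU-only correlations of −0.2 to −0.5. The adjusted effect falls from 0.53 to 0.18 in the equal-link example. These are illustrations, not forecasts for this trial.

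A reader might take biased treatment comparison to include the main result. It does not: the primary chi-square test uses neither variable, and the 70 per condition does not depend on them. The change should be made, but the trial's main conclusion does not hang on it.

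**What to change.** In the sixth anticipated problem of the Discussion, delete the statement that contact minutes and treatment period will be handled as moderating factors. State that moderators are limited to variables measured before randomisation, in line with the lists under Aim of the study and Secondary outcome measures.

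Report face-to-face minutes and duration descriptively by arm. If their role is of interest, analyse them only as post-randomisation process (mediating) variables, labelled exploratory and with the assumptions written down.

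The cost is a change of wording, and data collection stays as it is. The small downside is that the trial gives up a moderator-style answer on unequal contact.
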